## Abstract

**Background:** Prior laboratory findings indicate that training avoidance movements to angry faces may lower anger and aggression among healthy participants, especially those high in trait anger. To enrich this training and make it more suitable for clinical applications, it has been developed into a Virtual Reality Game for Aggressive Impulse Management (VR-GAIME).

**Methods:** The proposed study will examine the effects of this training in a randomized controlled trial among forensic psychiatric outpatients with aggression regulation problems (*N* = 60). In addition to the aggression replacement training, participants will play either the VR-GAIME or a control game. Anger will be assessed using self-report. Aggressive impulses will be measured via self-report, a validated laboratory paradigm, and rated by clinicians.

**Discussion:** The authors hypothesize that the combination of the VR-GAIME and regular aggression treatment will be more successful in reducing aggressive behavior. One of the strengths of the proposed study is that it is the first to examine the effects of a motivational intervention in a clinical sample characterized by problems in regulating anger and aggression. Another strength of the proposed study is that the VR-GAIME will be implemented as a multi-session intervention. Additionally, the VR-GAIME applies, for the first time, serious gaming and virtual reality on an avoidance motivation intervention. If positive results are found, the VR-GAIME may be systematically deployed in forensic psychiatric settings.

**Trial registration**: The trial is registered with The Netherlands National Trial Register, number: NTR6986.

## Introduction

Anger and aggression are common to all individuals, however, when it occurs frequently, increases in severity and it disrupts ones functioning, it becomes a significant problem (1). Anger is an acute emotional-physiological reaction that ranges from mild irritation to intense fury and rage (i.e., state anger). The disposition to experience state anger with greater frequency and intensity is referred to as trait anger (2, 3). When anger is not controlled or regulated appropriately, it increases the risk of aggressive behavior (4–6). Aggressive behavior is defined as a destructive behavior directed to another person, object or animal with the intention to cause harm and can be divided into in impulsive (affective, reactive) or instrumental (predatory, proactive) subtype (7, 8).

Aggression in general, and especially the impulsive subtype, is related to poor emotion regulation and poor impulse control (5, 6, 9). Aggressive behavior also has a clear link with antisocial behavior, and is a common basis for referral to forensic psychiatric institutions. Therefore, in treating antisocial and aggressive behavior, much attention has been paid to the importance of emotion regulation and self-control (10–12).

Interventions based on principles of Cognitive-Behavioral Therapy (CBT) have traditionally been the interventions of choice in treating aggression regulation problems (13, 14). These interventions, however, are only partially successful in reducing aggressive behavior and usually only beneficial to a subgroup of individuals (10, 13, 15, 16). Furthermore, CBT interventions appeal to abilities such as reflection, introspection and willingness to genuinely talk about problems in controlling anger and/or aggression. However, these capacities are often limited in individuals with anger or aggression management problems [e.g., (17, 18)]. Additionally, CBT-based interventions target more conscious, deliberate responses, and thus may have little impact on underlying implicit or automatic characteristics (19). When left untreated, these underlying factors might re-emerge during highly provoking and frustrating situations (20). As such, there is room for improvement of traditional aggression regulation interventions.

One new approach focuses on the motivational underpinnings of aggression regulation (21). People high in trait anger tend to have high levels of approach motivation (22), especially in situations when they are socially provoked (21). Which means that, in general, they have an automatic approach tendency toward potential social threat. Furthermore, experiments have shown that blocking approach motivation, for instance, by changing people's posture, can lower state anger and aggression (21). These findings suggest that a motivational approach could contribute to anger and aggression regulation among high-risk populations.

Initial experiments suggest that the motivational approach to anger management can be turned into an intervention (23). These experiments made use of an adapted joystick task that was validated in previous motivational intervention research in the treatment of alcohol abuse and social anxiety (24–26). These studies already proved that such an approach bias modification was successful in reducing alcohol consumption in heavy drinkers and emotional vulnerability in socially anxious individuals. In the experiments by Veenstra et al. (23), healthy participants were asked to perform a task in which they responded to angry or happy faces with a joystick. In the avoidance training condition, participant made avoidance movements to angry faces. In the control condition, participant made approach movements to angry faces. The results showed that after avoidance training, participants reported less angry feelings and expressed less aggressive impulses. These findings were most evident among individuals high in trait anger, who are characterized by the disposition to experience state anger with greater frequency and intensity (2, 3). These results suggest that reducing approach motivation toward social threatening stimuli could be an important addition to conventional anger and aggression regulation interventions.

Although the aforementioned findings are promising, they are limited in important ways. First, the avoidance training of Veenstra et al. (21) consisted of a single session. To increase the long-term effects of the training, its effects should be examined across multiple sessions. Second, the avoidance training was investigated among healthy undergraduate students who were not characterized by severe levels of anger and/or aggressive behavior. To elucidate the clinical relevance of motivational training, its effects among clinical populations need to be investigated. Third and last, the avoidance training of Veenstra et al. (21) used a joystick task that was not very engaging for participants, which could hinder implementation in clinical settings. Especially among individuals receiving treatment for anger and aggression regulation problems, treatment motivation is often lacking (17, 27). To warrant sufficient treatment motivation, it would be desirable to develop a more engaging variant of the motivational training.

For increasing treatment motivation, interventions that use serious gaming and virtual reality technology have been found to be highly effective (28). Serious games refer to games that do not have fun, enjoyment or entertainment as primary purpose but rather training, education or health improvement (29, 30). By introducing playful and interactive elements in an intervention, serious gaming may enhance motivation of the target group (28). Virtual reality (VR), on the other hand, makes use of virtual environments to present digitally recreated real world activities to participants via non-immersive and immersive mediums which can be systematically manipulated to be relevant to patients' problems (31, 32). Another advantage is that VR gives the unique opportunity to investigate and treat underlying behavioral mechanisms in controlled experimental designs that nonetheless possess high ecological validity.

Initial studies of serious gaming and VR in psychiatric treatments have found that these techniques can be used to successfully reduce aggressive behavior, impulsivity, anxiety, posttraumatic stress symptoms and to improve self-regulation and pro-social behavior (33–37). Serious gaming and VR are thus promising tools for enhancing the impact of psychological interventions and have also gained recognition in forensic psychiatry (38). A VR aggression prevention training is even developed and currently examined among forensic psychiatric patients (39).

For the current study, we combined the motivational modification paradigm (21), serious gaming, and VR technology to create a new treatment tool for the treatment of aggressive behavior: the Virtual Reality Game for Aggression Impulsive Management (VR-GAIME). The VR-GAIME is based on the approach-avoidance modification paradigm that was investigated by Veenstraet al. (21). Instead of joystick movements, however, the VR-GAIME manipulates whole body movements in an immersive environment. During the VR-GAIME, each participant gets assigned to the role of a courier who has to collect packages in a shopping street. In the shopping street, the participant is met by avatars who are acting in either an agreeable or disagreeable manner. Agreeable avatars have a happy or neutral facial expression and are saying pleasant things (e.g., “Have a nice day,” “You are wearing such a nice shirt!”). Disagreeable avatars, by contrast, have an angry facial expression and are saying unpleasant things (e.g., What are you looking at? “Get out of my way!”).

The VR-GAIME will be administered during multiple sessions alongside Aggression Replacement Training (ART) among forensic psychiatric outpatients with aggression regulation problems. Patients will be randomly allocated to the VR-GAIME (experimental training condition) or a placebo game (control training condition). In the experimental training condition, patients will be instructed to lean forward (i.e., make an approach movement) in response to agreeable avatars and to lean backwards (i.e., make an avoidance movement) in response to disagreeable avatars. Patients in the experimental training condition will be trained to respond with avoidance behavior to anger-relevant situations. In the control condition, patients will play the same game as patients in the experimental condition. However, patients in the control group will not encounter any disagreeable avatars and will hence not receive any training about anger-relevant situations.

The aim of the current randomized controlled trial is to investigate the effect of the VR-GAIME tool in combination with ART on the level of aggressive behavior of forensic psychiatric outpatients. Anger and aggressive impulses will be measured using self-report and a validated laboratory paradigm as well as by clinician ratings. Also, approach and avoidance behaviors will be assessed using self-report. Additionally, drop-out rates among outpatients receiving aggression treatment are high (40) and is associated with psychopathy and proactive aggression (41, 42). To determine whether drop-out is in line with previous studies or might be less/higher due to the game, we include measures of psychopathy and aggression subtype. Finally, aggression treatment might also change other emotions than anger. To examine this notion a self-report measure for distinct emotions will be included. Also, the effects might be associated with other biases in processing facial expression. To explore this notion, a measure for a hostile interpretation bias will be included. We hypothesize that the combination of the VR-GAIME and ART will be more successful in reducing anger and aggressive behavior relative to the control condition.

## Methods

### Design

The design will be a double blind randomized controlled trial. The trial consists of two conditions: (1) ART and the VR-GAIME; (2) ART and the VR placebo game. Assessments will take place pre-treatment (T1), halfway (T2), and post-treatment (T3). The sample size was calculated for the main research question using G^*^Power software. The sample size was calculated for a two (group: ART and VR-GAIME vs. ART and placebo game) × 3 (assessment: pre vs. halfway vs. post) interaction, with the assumption of a small-to-medium effect size (*eta*^2^ = 0.08) and a power of 1–β = 0.80. This has led to a minimum required sample size of 60.

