Instead of the active (experimental) game, half of the participants will play a placebo game. In terms of the general game elements, the placebo game is identical to the original game. The only difference is that, in the placebo game, no disagreeable avatars will appear. As a consequence, avoidance behavior will not be trained in the placebo/control condition. The instruction patients will receive is comparable. This setup was chosen to avoid that patients easily can find out in which condition they participated. Based on prior studies we know that patients tend to discuss such experiences once they participate in group treatment. Participants will be randomly allocated to an experimental or a control condition. Both versions of the game have a maximum duration of 30 min. The two versions of the game are referred to as game 1 and game 2 on the VR computer. Furthermore, the researcher takes position behind the computer screen in order to stay blind for the condition.

Besides the packages and the avatars in the shopping street, the participant will also come across litter on the street. The participant has to make sure he will not walk into this litter otherwise he will lose a package. Thus, when confronted with litter, the participant has to pick up the litter and deposit it behind him. The latter game element is introduced to make the game more varied and engaging.

An additional game element consists of mini-game is an extra challenge and is included to make the game more varied for players. Participants gain entry to the mini-game by collecting bonus packages, which appear as more colorful and somewhat smaller as the regular packages. Once enough bonus packages are collected, the mini-game can be played. During the mini-game, the participants stand underneath a window from which packages are thrown down. Participants need to catch these fallen packages. The higher the level, the more difficult the mini-game will be: The packages will fall faster as well as some rubbish will be thrown out of the window which should not be caught.

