### Statistical Analyses

This RCT has a repeated-measures design with both between- and within-subject variables. The main between-subject factor is experimental condition: ART + VR-GAIME vs. ART + VR placebo game. The main within-subject factor is assessment time: aggressive behavior at pre-intervention (T1), halfway (T2), and post-intervention (T3). To examine whether aggressive behavior will change over time, a linear mixed model will be used (SPSS, version 25). One advantage of this analysis is that it is possible to include individuals with incomplete data, without imputing data (65). This method was favored because there is a plausible chance that the halfway and/or end-of-treatment measurements will not be completed by all participants, given that dropout rates in forensic psychiatric settings are usually high.

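### The assumed interaction effect (eta² = 0.08) is labelled small-to-medium but lies somewhat above medium, so the power statement claims a sensitivity that N = 60 does not have

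*Protocol article*

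**What the plan says.** The Design section of the protocol article states that "The sample size was calculated for the main research question using G^*^Power software". The effect tested is the interaction of two groups with three assessments, "3 (assessment: pre vs. halfway vs. post) interaction". The calculation is done "with the assumption of a small-to-medium effect size", with eta² = 0.08 in the bracket that follows, "and a power of 1–β = 0.80". The result: "This has led to a minimum required sample size of 60".

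The VR-GAIME section implies equal arms: "Instead of the active (experimental) game, half of the participants will play a placebo game".

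The article does not say what it means by small or medium and does not give a basis for 0.08. It does not state alpha, the G*Power effect-size option or the assumed correlation between assessments. A full protocol may hold these, so their absence is not the point here. The point is that the label and the number printed beside it disagree.

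**The concern.** A sample-size statement tells the reader which effects the trial can detect. This one says that 60 patients give 80% power for a small-to-medium effect. On the benchmarks normally used for this type of calculation, eta² = 0.08 is larger than that.

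Interpretation is what is at stake. Both arms receive Aggression Replacement Training, and the two games differ only in the disagreeable avatars. The Discussion concedes that the control game may itself have positive effects. A modest added benefit is therefore a realistic possibility. A reader who trusts the label could take a non-significant interaction as evidence against such a benefit, when the trial had little chance of showing it.

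**Working it through.** **Inputs.** From the article: eta² = 0.08, power 0.80, 2 groups × 3 assessments, N = 60 (Design); equal arms (VR-GAIME section). Assumed, because not stated: alpha 0.05, sphericity, no dropout. The benchmarks f = 0.10 / 0.25 / 0.40 are the usual convention and do not come from the article.

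**1. Convert the effect size.** f² = eta²/(1 − eta²) = 0.08/0.92 = 0.0870, so f = 0.295. The benchmarks on the eta² scale, from f²/(1 + f²), are 0.01/1.01 = 0.0099, 0.0625/1.0625 = 0.059 and 0.16/1.16 = 0.138. So 0.08 lies above medium, about a quarter of the way to large: (0.08 − 0.059)/(0.138 − 0.059) = 0.27.

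**2. Reproduce N = 60.** Use the noncentral F test with df1 = (2 − 1)(3 − 1) = 2 and df2 = 2(N − 2). With eta² as a partial eta² (G*Power's SPSS option), λ = f² × (N − 2) × 2. At N = 60, λ = 0.0870 × 58 × 2 = 10.09, df2 = 116, the critical F is 3.07 and power is 0.808. The smallest N with equal arms is 60, which is the article's figure. The Cohen option (λ = f² × N × 2) gives 58, and power 0.822 at N = 60. G*Power's 3.0 option, λ = f² × N × 3/(1 − ρ), needs only 40, 28, 22 or 14 patients at ρ = 0, 0.3, 0.5 or 0.7 for f = 0.295, so it was not the basis. Alpha 0.10 gives 46 to 48 and does not fit either.

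**3. Power of N = 60 over the range that the label names** (SPSS option):

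| partial eta² | f | λ | power at N = 60 | N for 80% power, equal arms |
|---|---|---|---|---|
| 0.01 | 0.10 | 1.17 | 0.15 | 482 |
| 0.02 | 0.14 | 2.37 | 0.26 | 240 |
| 0.03 | 0.18 | 3.59 | 0.37 | 160 |
| 0.04 | 0.20 | 4.83 | 0.48 | 120 |
| 0.06 | 0.25 | 7.40 | 0.67 | 80 |
| 0.08 | 0.29 | 10.09 | 0.81 | 60 |

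The Cohen option changes these powers by at most 0.02. Power reaches 50% at eta² = 0.041 (Cohen) to 0.042 (SPSS), and 80% only at 0.076 to 0.079.

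**4. The same effect in SD units.** With 30 per arm and compound symmetry, λ = 15 × S × d²/(1 − ρ). Here d is the arm difference at T3 in SDs, and S is the sum of squared deviations of the effect pattern over the three assessments: 0.5 if the difference grows linearly, 0.667 if it is fully present from T2. Setting λ = 10.09 gives d = √[10.09(1 − ρ)/(15S)].

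| ρ | d, step | d, linear |
|---|---|---|
| 0.5 (assumed) | 0.71 | 0.82 |
| 0.651 | 0.59 | 0.69 |
| 0.82 | 0.43 | 0.49 |

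The last two correlations are the ends of the intraclass range that the Primary Outcome Measure section gives for the self-rated SDAS.

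**The case against.** **Nothing was miscalculated, and the exact value stands next to the adjective.** This stands. N = 60 follows from eta² = 0.08, and a careful reader can see what was assumed. A reader might infer from the label that the sample size is wrong. The article does not support that, because the number, and not the label, went into the calculation.

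**The label depends on the metric.** Relative to the within-cell SD, as in G*Power's 3.0 option, the same alternative is f of about 0.17 at ρ = 0.5, 0.14 at 0.65 and 0.10 at 0.82. Those values could fairly be called small or small-to-medium. But the article states eta², and its N is reproduced only when 0.08 is read as a partial eta², so the label has to be judged on that scale.

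**Medium-to-large would overshoot in the other direction.** This stands. On the f scale, 0.295 is 0.045 above medium and 0.105 below large.

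**It is too strong to say that the trial would usually miss small-to-medium effects.** This stands in part. Below eta² of about 0.041 the trial is more likely to miss the effect than to find it, but at the medium benchmark power is about two thirds.

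**The implied difference need not be large in SD terms.** A reader might infer that the trial relies on an arm difference of 0.6 to 0.8 SD. That holds only for between-wave correlations at or below the bottom of the SDAS stability range. Over the whole range it is 0.43 to 0.69 SD. A test-retest figure may overstate the correlation across 12 weeks of treatment, so 0.82 may be optimistic, but it cannot be left out.

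**No passage says that a null result would exclude a modest benefit.** True. The misreading is a risk that the wording creates, not a claim that the article makes.

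**Conclusion.** The point holds as a mislabelled assumption, not as an error in the sample size. Partial eta² = 0.08 is somewhat above medium by convention, and N = 60 is right for it (power 0.81). The trial does not have 80% power anywhere in the small-to-medium range: power runs from about 0.15 at eta² 0.01 to about 0.67 at 0.06, and is below one half for eta² under about 0.041.

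This rests on alpha 0.05, sphericity, equal arms and complete data, and on benchmarks that the article does not itself cite. Complete data is the favourable case: the Statistical Analyses section expects missing assessments, "given that dropout rates in forensic psychiatric settings are usually high". The choice between the SPSS and Cohen options does not change the conclusion. The SD translation depends on an unstated correlation and should not carry the argument.

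**What to change.** Keep N = 60. In the Design section, describe the assumption as a medium or slightly larger interaction (partial eta² = 0.08, f = 0.29). Add one sentence giving the power at N = 60 for a truly small-to-medium effect, about 0.37 at partial eta² 0.03, and say that a non-significant interaction would not exclude a benefit of that size. Stating alpha and the G*Power option in the same sentence would let a reader reproduce the figure.

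If an SD equivalent is given, show how it depends on the between-wave correlation: about 0.43 to 0.69 SD at T3 for correlations of 0.82 down to 0.651, and 0.71 to 0.82 SD at 0.5.

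This is a wording change. It needs no extra patients and leaves the design and analysis as they are. The only downside is a less favourable, but accurate, sensitivity statement.

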## Discussion

One of the strengths of the proposed study is that it is the first to examine the effect of a motivational intervention in a clinical sample characterized by problems in regulating anger and aggression. Previous studies on the effects of avoidance training on anger and aggressive impulses consisted of a single session joystick training among undergraduate students (23). The automatic approach of social threat displayed by individuals high in trait anger (21) might be more persistent among forensic psychiatric patients typified by higher levels of trait anger and problems with aggression regulation. In this regard, a single session might not be sufficient. Another strength of the proposed study is that the VR-GAIME will be implemented as a multi-session intervention. This also provides the unique opportunity to investigate motivational tendencies over a longer period of time. The proposed study will, therefore, have important theoretical implications, by providing a further test of motivational models of anger management (68).

Additionally, the proposed study makes use of innovative technologies. The VR-GAIME applies, for the first time, serious gaming and virtual reality on an avoidance motivation intervention. These techniques require more patient engagement. Furthermore, automatic processes are trained in more life-like situations which likely increases the ecological validity of the intervention. Another advantage of these techniques is that it provides an opportunity to develop a training tool that patients like to use. Treatment dropout in forensic psychiatric settings is extremely high (40). This might be due to high psychopathic traits and proactive aggression, but also the low levels of treatment motivation may play a role. It is conceivable that, once patients enjoy playing the game, they tend to dropout less end may benefit more from treatment.

One of the limitations of the proposed study is that, even though the control game does not train avoidance behavior, it does train approach behavior toward agreeable avatars. It may be that the control condition also will have positive effects. Additionally, patients will participate voluntarily, which means that it is possible that the most severe patients may not be included as they are not willing or capable to participate. This could introduce a selection bias that might limit the generalizability of the results.

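### The 0.80 power at N = 60 is a complete-data figure with almost no slack, while the plan itself expects missing T2 and T3 assessments

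*Protocol article*

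**What the plan says.** The Design section of the protocol article reports a G*Power calculation for the main research question. The tested effect is group (two levels) by "3 (assessment: pre vs. halfway vs. post) interaction". The calculation was made "with the assumption of a small-to-medium effect size", given as eta² = 0.08, "and a power of 1–β = 0.80". The result: "This has led to a minimum required sample size of 60". Alpha, sphericity and the G*Power effect-size option are not stated, and no allowance for loss is mentioned.

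The Abstract gives the trial size as the same N = 60.

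The Statistical Analyses section chooses a linear mixed model because it can use patients with incomplete data without imputation. The reason is that some patients may well miss the halfway or end-of-treatment measurement, "given that dropout rates in forensic psychiatric settings are usually high". The Introduction calls drop-out from outpatient aggression treatment high, and the Discussion calls treatment dropout in forensic psychiatric settings extremely high. No rate is given anywhere.

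**The concern.** The required number and the planned number are the same 60, but they may refer to different things. The calculation assumes three assessments for every patient, whereas the plan expects that some patients will not provide them. If so, the 0.80 belongs to a data set that the plan does not expect to obtain.

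This affects the primary test. If the comparison of the two games is not significant, a reader who trusts the printed power will take it as fairly strong evidence against an effect of the assumed size. Lower true power makes that inference weaker, and the article does not let the reader see by how much.

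**Working it through.** **Inputs.** From the Design section: 2 groups, 3 assessments, eta² = 0.08, power 0.80, N = 60. From the description of the placebo game: half of the patients in each condition. Assumed because not stated: alpha 0.05, sphericity, all dropout rates.

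**Step 1: reproduce the 60.** f² = 0.08/0.92 = 0.0870 (f = 0.295). The test has df1 = (2 − 1)(3 − 1) = 2 and df2 = 2(N − 2), with a noncentral F.

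- SPSS-type option, λ = f² × (N − 2) × 2. At N = 60, λ = 0.0870 × 58 × 2 = 10.09, df2 = 116, power 0.808. N = 59 gives 0.801 and N = 58 gives 0.793. The smallest equal-arm total reaching 0.80 is therefore 60.
- Cohen option, λ = f² × N × 2. At N = 60, λ = 10.43, power 0.822. N = 57 gives 0.800 and N = 56 gives 0.793.
- Correlation-based default, λ = f² × N × 3/(1 − ρ). The equal-arm totals are 40, 28, 22 and 14 for ρ = 0, 0.3, 0.5 and 0.7. None is near 60, so this is not the calculation reported.

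Either option that fits the printed figure counts complete patients. The slack is one patient (60 − 59) or three (60 − 57).

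**Step 2: completers only, as a lower reference.** The same formula (SPSS-type option) at 60 × (1 − loss):

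| Loss | Complete patients | Power at eta² = 0.08 | eta² detectable with power 0.80 |
|---|---|---|---|
| 20% | 48 | 0.70 | about 0.10 |
| 30% | 42 | 0.64 | about 0.11 |
| 40% | 36 | 0.56 | about 0.13 |

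This is not the planned analysis, which keeps partial records.

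**Step 3: mixed model keeping partial records.** Assume 60 enrolled, T1 complete, monotone loss, data missing at random, and equal correlation ρ between assessments (the structure that a random intercept implies). The information matrix for each arm is summed over three patterns (T1 only; T1 and T2; all three). Its inverse gives the variance of the two group-by-time contrasts, T2 − T1 and T3 − T1. Let r be the noncentrality with loss divided by that without loss. Then λ = r × 10.09, and df2 = observations − 60 − 4.

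Worked case: 30% lost by T3, half of them before T2, ρ = 0.5, effect growing linearly. The observations number 60 × (1 + 0.85 + 0.70) = 153, so df2 = 89. r = 0.776, λ = 7.83, power 0.692.

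The table gives the range over ρ = 0.5 and 0.7, three effect shapes (linear; complete by T2 and sustained; at T3 only) and two timings of loss (half before T2; all after T2):

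| Lost by T3 | SPSS-type option | Cohen option |
|---|---|---|
| 10% | 0.765–0.798 | 0.779–0.812 |
| 20% | 0.713–0.787 | 0.728–0.802 |
| 30% | 0.652–0.776 | 0.667–0.791 |
| 40% | 0.581–0.763 | 0.597–0.778 |

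The upper ends come from an effect complete by T2 with loss only after T2; the lower ends come from an effect at T3 only. The correlation matters little: at 20% loss with a linear effect and half of the loss before T2, power is 0.737 at ρ = 0.5 and 0.731 at ρ = 0.7.

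**The case against.** Several points on the other side have weight.

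- **No figure is miscalculated.** The 60 reproduces, and a condensed article may leave an attrition allowance to the full protocol. That rules out a complaint about a missing detail. The tension within the printed text remains: a complete-data 60, the same 60 as trial size, and an expectation of incomplete data. The article does not say outright that 60 is the number randomised, but it names no larger enrolment target.
- **The mixed model was chosen for this problem.** It helps, and Step 3 credits it. It uses the T1 and T2 values of patients who leave later, but cannot recreate their T3 values.
- **Treatment dropout is not the same as a missed assessment.** The Introduction and the Discussion speak of the former, and the Discussion suggests that the game might reduce it. The Statistical Analyses section, however, itself gives dropout as the reason for expecting missed measurements.
- **The favourable scenario is plausible.** The game ends at T2, so the effect might be complete by then. With losses only after T2, power at 20% loss is 0.787 (SPSS-type option) or 0.802 (Cohen option).

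A reader might infer that 0.80 holds only if all 60 patients complete. That is too strong, because there is slack of one to three patients and the favourable scenario keeps power near 0.80. A reader might also infer that the trial has little better than even odds of detecting its target effect. That comes mainly from completers-only power at 40% loss or more, which is neither the planned analysis nor a rate that the document states.

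**Conclusion.** The point holds in a limited form. The printed 0.80 describes 60 patients with complete data, and under the plan's own expectation of missed T2/T3 assessments the design is unlikely to deliver it.

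The size cannot be fixed from the document. At 10% loss the SPSS-type option loses about 1 to 4 points from 0.808; at 30% loss it loses about 3 to 16 points. Every SPSS-type scenario with 10% or more lost falls below 0.80. The Cohen option runs about 1 to 2 points higher. At 10% loss it reaches about 0.80 or a little more if the effect is complete by T2. At 20% it does so only if, in addition, losses come after T2. At 30% and above no scenario examined reaches 0.80.

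These results rest on alpha 0.05, sphericity, missingness at random, and the assumed dropout rates, effect shapes and loss timings. The direction is secure in most scenarios; the amount is not. This is a statement of power that does not match the expected data, not an error of arithmetic.

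**What to change.** In the Design section:

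1. Say that 0.80 applies to 60 patients with all three assessments, and name the alpha, the sphericity assumption and the G*Power effect-size option used.
2. State the rate of missing T2 and T3 assessments that the clinic expects.
3. Restate the power and the detectable eta² for 60 enrolled under the planned mixed model at that rate, showing the assumed correlation, effect shape and timing of loss. The ranges above show the scale, but the sponsor should compute its own figures.

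This changes wording only. The stated power becomes somewhat less favourable, and no extra patients are needed.
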